**Methods/Design:**

The trial is being conducted at 10 sites across the UK. Seven hundred participants and their families will be recruited and randomised on a 1:1 basis to multisystemic therapy or management as usual. Treatments are offered over a period of 3 to 5 months, with follow-up to 18 months post-randomisation. The primary outcome is out-of-home placement at 18 months. Secondary outcomes include offending rates, total service and criminal justice sector costs, and participant well-being and educational outcomes. Data will be gathered from police computer records, the National Pupil Database, and interview and self-report measures administered to adolescents, parents and teachers. Outcomes will be analysed on an intention-to-treat basis, using a logistic regression with random effects for the primary outcome and Cox regressions and linear mixed-effects models for secondary outcomes depending on whether the outcome is time-to-event or continuous.

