**Figure 1 F1:**
[figure not shown]
**CONSORT flow diagram of progress through the phases of recruitment and treatment in the START trial of multisystemic therapy.** CAMHS, child and adolescent mental health services; MAU, management as usual; MST, multisystemic therapy.

Assuming that 30% of the MAU arm will have out-of-home placements, this sample size will give 86% power to detect a 10% difference in out-of-home placements (a reduction from 30% to 20%). To take account of within-therapist correlation of outcomes in the MST arm, an intraclass correlation of 0.02 and a total of 30 therapists has been assumed, giving design effects of 1.22 in the MST arm and 1.0 in the MAU arm, and thus reducing the power to 83%.

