#### Primary outcome

The primary analysis will be a logistic regression with random effects to account for clustering by therapist. The analysis will include centre, number of past convictions, gender, age at onset of criminal behaviour and other risk indicators as fixed effects. The logistic regression will be fitted using generalised estimating equations. A Wald test of the effect of intervention will be used as the primary analysis. As a secondary analysis, tests of interaction will be used to explore whether the intervention differs according to gender, age, presence of a criminal record or referral path. Clustering by therapist will be accounted for by computing robust standard errors [102].

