#### Secondary outcomes

The antisocial behaviour outcome (time to offence) will be analysed using a Cox regression. All other secondary outcomes will be modelled using linear mixed-effects models, with separate treatment effects for the 6-, 12- and 18-month outcomes and an unstructured covariance matrix. The effect of intervention on the 18-month outcome will be tested using a Wald test. Tests of interaction will be performed for all secondary outcomes in which a nominally significant treatment effect is found.

It is anticipated that the primary outcome will have very little missing data as these data are obtained independently of the participants. For the secondary outcomes, linear mixed models and Cox regression yield valid inferences when data are missing at random (that is, the probability of a particular data point being missing depends only on observed data). It is possible that data may be missing not at random, so sensitivity analyses will be conducted to explore the impact of missing data.

There is just one primary outcome, so the primary analysis will be conducted at a nominal two-sided significance level of 0.05. There are several secondary outcomes, so caveats will be used when interpreting effects of treatment on secondary outcomes. No formal correction for multiple testing will be used.

There is no plan to analyse outcomes by site and it is hoped that TAM-R scores will pick up the variance associated with individual therapists.

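### The primary Wald test relies on robust standard errors with about 30 therapist clusters, all in one arm, and states no small-sample correction; in its usual default form it would run at about 6–7.5%, not 5%

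*Protocol article*

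**What the plan says.** The protocol article's statistical analysis plan, under Primary outcome, sets out the main analysis:

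- Fitting: "The logistic regression will be fitted using generalised estimating equations".
- Fixed effects: "The analysis will include centre, number of past convictions, gender, age at onset of criminal behaviour and other risk indicators as fixed effects". There are 10 sites.
- Test: "A Wald test of the effect of intervention will be used as the primary analysis".
- Variance: "Clustering by therapist will be accounted for by computing robust standard errors", with a literature reference but no named variant, correction or degrees of freedom.

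The same paragraph also describes the model differently: "The primary analysis will be a logistic regression with random effects to account for clustering by therapist".

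Under Secondary outcomes the level is fixed: "the primary analysis will be conducted at a nominal two-sided significance level of 0.05".

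Under Sample size and power calculation, "a total of 30 therapists has been assumed", with an intraclass correlation of 0.02 and design effects of 1.22 in the MST arm and 1.0 in the MAU arm. Study setting describes a team of four therapists at each site, which makes 40 over 10 sites.

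**The concern.** The sandwich variance estimates between-cluster variation from the observed cluster totals, and it is accurate when there are many clusters. Here the clusters that matter are 30 or 40 therapists, all in one arm, three or four to a centre. The model also estimates an effect for each centre. Those effects partly absorb the therapist deviations that the sandwich needs to see, so the estimated variance is biased downwards. It is also noisy, and a normal reference ignores that noise.

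The trial has one primary test and one alpha. If the test does not hold its level, a borderline result in favour of MST would be declared too readily and its confidence interval would be too narrow.

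**Working it through.** **1. The plan's own figures reproduce.** Inputs: 350 per arm, 30% v 20%, two-sided 0.05, 30 therapists, ICC 0.02.

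- Mean caseload 350/30 = 11.67. Design effect 1 + (11.67 − 1) × 0.02 = 1.213, or 1 + 11 × 0.02 = 1.22 with caseloads of 12.
- No clustering: null SE = √(2 × 0.25 × 0.75/350) = 0.03273; alternative SE = √((0.21 + 0.16)/350) = 0.03251; z = (0.10 − 1.96 × 0.03273)/0.03251 = 1.102; power 86.5% (stated 86%).
- With 1.22 in MST: null SE = √(0.1875 × 2.22/350) = 0.03449; alternative SE = √((0.21 + 0.1952)/350) = 0.03403; z = 0.952; power 83.0% (stated 83%).

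**2. Size if clustering is ignored.** The variance is understated by (1.22 + 1.0)/2 = 1.11. The effective critical value is 1.96/√1.11 = 1.860, so size is about 6.3%. This is the excess that the robust SE is meant to remove.

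**3. Simulated size of the default robust test.** Common set-up: 10 centres, MAU participants as singletons, ICC 0.02, centre fixed effects, ordinary sandwich clustered on therapist, critical value 1.96. Set A: null rate 25%, 35 per arm per centre, 6 further covariates, 12,000 trials per main setting. Set B: null rate 30%, 35 per arm per centre, 4 further covariates, 8,000 to 36,000 trials for main settings. Set C: a further check, 4,000 trials per setting.

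| Setting | A | B | C |
|---|---|---|---|
| 30 therapists, equal caseloads | 6.9% | 6.7% | 6.8% |
| 40 therapists | 6.5% | 6.0% (runs 5.5–6.5%) | 6.2% |
| 30 therapists, unequal caseloads | 7.4% | 7.6% | 6.3% |
| 30 therapists, null rate 20% | – | 6.6–7.0% | – |
| 30 therapists, no centre effects | – | 5.5% | – |
| 30 therapists, ignoring clustering | 6.7% | 6.2% (one run) | – |

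Monte Carlo SE is about 0.23 points for 12,000 trials and √(0.065 × 0.935/4000) = 0.39 points for 4,000. An exchangeable working correlation gave 6.8% with 30 equal-caseload therapists, so that choice does not remove the excess. The most adverse setting (unequal caseloads, ICC 0.05, 20% rate) reached 8.0%.

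**4. Why.**

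- Bias: in set A the mean robust SE was 0.178 against a true SD of 0.191, a ratio of 0.932 (about 7% too small). In set B the ratio was 0.945 (about 5% too small), and 0.986 without centre effects.
- Noise: take 30 − 10 = 20 degrees of freedom for the MST-arm variance and 349 for MAU. Satterthwaite gives 2.22²/(1.22²/20 + 1/349) = 63.8 df, and a 1.96 cut-off then has size 5.4%.
- Together: a cut-off of 1.96 × 0.945 = 1.852 on 63.8 df has size 6.9%, in line with the simulations.
- With ICC set to 0, the robust test still rejected 6.6%, against 5.3% for the model-based test. The excess comes from the variance estimator itself.

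**5. Corrected versions, 30 therapists.**

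| Method | Size | Power, 30% v 20% (set A) |
|---|---|---|
| Ordinary sandwich, normal | 6.7–6.9% | 86.3% |
| Kauermann-Carroll, normal | 5.3% (A), 5.1% (B) | 82.5% |
| Kauermann-Carroll, t on 29 df | 4.5% (A) | 79.9% |
| Mancl-DeRouen, normal | 4.1% (A), 3.8% (B) | – |
| Ordinary sandwich, t on 20 df | 5.0% (B) | – |

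Across settings, Kauermann-Carroll with a normal reference gave 4.6–5.6% in set C and 5.1–5.8% in set B. With unequal caseloads in set B, it gave 5.8% where the ordinary sandwich with t on 20 df gave 6.1%.

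**The case against.** The strongest reply is that the article nowhere says the standard errors are uncorrected or that the Wald statistic is referred to the normal distribution. Such details are often left to a full analysis plan, which is not at hand, and the ordinary sandwich with t on 20 df held 5.0% in the base case. This stands to the extent that a reader might infer that the plan has chosen an uncorrected estimator, and the text does not support that. The point is conditional on the default. It is still more than a missing detail: the article names the estimator, the test and the centre effects, and software given those instructions ordinarily produces the uncorrected version.

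Second, a reader might fix the size at one narrow value. The documents do not allow that. They leave open caseload balance, event rate under the null, the number of other risk indicators and whether there are 30 or 40 therapists. One 40-therapist run gave 5.5%, barely distinguishable from 5%.

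Third, the same paragraph describes random effects. Under that reading the sandwich would not be the main device for clustering. GEE fits no random effects and the paragraph's last sentence relies on robust standard errors, so the GEE reading is the natural one, but the contradiction is a separate matter to be reconciled.

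Finally, a reader might conclude that adjusting for therapist is pointless, because the default robust test rejects as often as no adjustment. That holds only near an ICC of 0.02, which is an assumption. The result argues for a better variance, not for ignoring clustering.

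**Conclusion.** The point holds in conditional form. If the robust standard error is the ordinary sandwich with a normal reference, the two-sided 5% test runs at about 6–7.5%: about 6.7% with 30 therapists and about 6% with 40. The interval is about 5–7% too narrow. At 6.7% that is roughly a third more false positives than intended (6.7/5 = 1.34). This rests on the GEE reading, an ICC of 0.02, MAU participants as singletons and fitted centre effects. The inflation is modest and does not invalidate the trial, but it affects the only primary test and is cheap to remove. Confidence is moderate.

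**What to change.** Under the statistical analysis plan's Primary outcome, specify a small-sample bias-corrected sandwich variance for the primary Wald test and its confidence interval, for example Kauermann-Carroll with a normal reference. Fix the reference distribution before unblinded analysis, because moving to t on 29 df takes simulated size from 5.3% to 4.5% and power from 82.5% to 79.9%. State that each MAU participant forms a singleton cluster, which the design effect of 1.0 already implies. Reconcile the random-effects wording with GEE in the same edit. If a correction is already intended, say which.

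The cost is a sentence or two of analysis wording and a slightly wider interval. Simulated power is about 82%, close to the stated 83%; the 86.3% of the uncorrected test comes partly from its inflated size.

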#### Secondary outcomes

The antisocial behaviour outcome (time to offence) will be analysed using a Cox regression. All other secondary outcomes will be modelled using linear mixed-effects models, with separate treatment effects for the 6-, 12- and 18-month outcomes and an unstructured covariance matrix. The effect of intervention on the 18-month outcome will be tested using a Wald test. Tests of interaction will be performed for all secondary outcomes in which a nominally significant treatment effect is found.

It is anticipated that the primary outcome will have very little missing data as these data are obtained independently of the participants. For the secondary outcomes, linear mixed models and Cox regression yield valid inferences when data are missing at random (that is, the probability of a particular data point being missing depends only on observed data). It is possible that data may be missing not at random, so sensitivity analyses will be conducted to explore the impact of missing data.

There is just one primary outcome, so the primary analysis will be conducted at a nominal two-sided significance level of 0.05. There are several secondary outcomes, so caveats will be used when interpreting effects of treatment on secondary outcomes. No formal correction for multiple testing will be used.

There is no plan to analyse outcomes by site and it is hoped that TAM-R scores will pick up the variance associated with individual therapists.

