#### Objective measures

Objective secondary outcomes will be collected from reports of offending behaviour based on police computer records, including details of custodial sentences. These measures will be taken at 6-monthly intervals, for the 6 months before randomisation, the 6 months covering the intervention period, and 6-monthly until the 18-month follow-up point. The number of records of offending behaviour (count data) will be obtained and 6-month periods free of any offending behaviour will also be recorded (binary data). Records are obtained from the Police National Computer as well as from the Young Offender Information System database at each site; these records detail information on offences, court appearances, criminal orders, police custody records and arrest rates.

Records of school attendance and exclusions will be retrieved from both the local schools themselves and the National Pupil Database to assess educational outcomes.

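### The plan assigns two police-record outcomes, which it labels count and binary data itself, to linear mixed models

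*Protocol article*

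**What the plan says.** In the protocol article, the Objective measures section introduces the police-record data as secondary outcomes: "Objective secondary outcomes will be collected from reports of offending behaviour based on police computer records, including details of custodial sentences". They are taken for the 6 months before randomisation and then 6-monthly to 18 months. The section gives the type of each derived variable. The first is a tally: "The number of records of offending behaviour (count data) will be obtained". The second is a yes/no indicator for each window: "6-month periods free of any offending behaviour will also be recorded (binary data").

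Under Statistical analysis plan, Secondary outcomes, one offending variable has its own model: "The antisocial behaviour outcome (time to offence) will be analysed using a Cox regression". Everything else falls under one rule: "All other secondary outcomes will be modelled using linear mixed-effects models". Under that rule each follow-up visit gets its own treatment effect, the covariance matrix is unstructured, and a Wald test is applied to the 18-month effect. The same section orders interaction tests for every secondary outcome that shows a nominally significant treatment effect.

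The Methods/Design part of the abstract says that Cox and linear mixed models are used for secondary outcomes "depending on whether the outcome is time-to-event or continuous". Logistic regression is named only for the primary outcome. No count model is named anywhere.

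**The concern.** The data types and the assigned model do not match. A linear mixed model assumes normal errors whose variance does not depend on the fitted mean. For a 0/1 indicator the variance is p(1 − p). For offence counts it rises with the mean, usually faster than Poisson. An unstructured covariance matrix lets the variance differ by visit, but not by expected level within a visit.

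Three consequences follow:
- The count effect is reported as a difference in mean records, which a few prolific offenders can move, rather than as a rate ratio.
- The binary effect is a linear probability. Once covariates enter, fitted values can leave the 0 to 1 range.
- The planned interaction tests depend on the additive scale, so they can signal effect modification that is only a difference in baseline offending.

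The Discussion treats offending rates as a key measure of whether the intervention works, so these outcomes will be read closely.

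**Working it through.** **1. The plan's own figures.** No figure is given for the offending outcomes. The only power figures concern the primary outcome, and they reproduce. Inputs: 350 per arm, 30% versus 20%, two-sided 0.05.
- SE under the null: √(2 × 0.25 × 0.75 / 350) = 0.0327. SE under the alternative: √((0.21 + 0.16) / 350) = 0.0325.
- Power = Φ((0.10 − 1.96 × 0.0327) / 0.0325) = 86.5%, against the stated 86%.
- Design effect = 1 + (350/30 − 1) × 0.02 = 1.213, against 1.22. With the MST arm reduced to 350/1.22 = 287, power is 82.6%, against 83%.

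Nothing here is in question.

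**2. Outcome type against assigned model.**

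| Police-record outcome | Type stated | Model under the analysis section | Category in the abstract |
|---|---|---|---|
| Time to offence | time-to-event | Cox | yes |
| Number of offending records | count | linear mixed | none |
| Offence-free 6-month period | binary | linear mixed | none |

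**3. Does the linear test fail for counts?** The document gives no offence rate or dispersion, so these are assumptions: negative binomial counts in one 6-month window, mean 0.5 or 1, dispersion 2 or 4, 350 per arm, 4,000 runs. The rate ratio of 0.72 is also an assumption; it borrows the pooled risk ratio for dichotomous outcomes quoted in the Background.
- Linear: z = (mean A − mean B) / √((s²A + s²B)/350). With equal arms, the pooled-variance form gives the same standard error.
- Negative binomial: z = log(mean A / mean B) / √((1/mean A + k)/350 + (1/mean B + k)/350), with dispersion k taken as known.

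| Mean, dispersion | Type I error, linear / NB | Power at 0.72, linear / NB |
|---|---|---|
| 0.5, 2 | 4.9% / 4.9% | 54.2% / 54.2% |
| 1, 2 | 5.3% / 5.2% | 68.4% / 68.9% |
| 1, 4 | 5.2% / 5.1% | 47.3% / 48.1% |

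A smaller run (600 replicates) adjusted for the baseline count. Type I error was 3.5% and 4.3% (linear) against 4.0% and 6.5% (NB). Power was 63.7% and 54.7% against 65.3% and 52.3%. Simulation error at a 5% rate with 600 runs is √(0.05 × 0.95/600) = 0.9 points, so neither method is clearly ahead. Therapist clustering, repeated visits and the binary outcome were not simulated.

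**4. The effect scale and the interaction tests.** Take one rate ratio of 0.72 in two subgroups with assumed mean counts of 2.0 and 0.4.
- Differences: 2.0 × 0.28 = 0.56 and 0.4 × 0.28 = 0.11.
- The relative benefit is identical, yet the additive model shows a five-fold difference in effect.

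Unequal baseline offending is plausible here: youth offending team referrals must have a record of convictions or formal warnings, while the criteria for the other three referral routes do not require a conviction.

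**The case against.** **The abstract restricts linear models to continuous outcomes.** Read with the analysis section, that arguably leaves count and binary outcomes unassigned, which a condensed article may leave to a fuller plan. The abstract does point to the better rule. The analysis section, however, is the more specific text, and it covers all remaining secondary outcomes. On either reading, two outcomes defined in the article lack a suitable model.

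**No inferential harm is shown.** For counts this largely stands. With separate effects per visit in a randomised trial, a mean difference or a risk difference is interpretable, and out-of-range fitted values do not invalidate the contrast. A count model also does not remove the influence of prolific offenders: without covariates, the negative binomial ratio is the ratio of the same two arm means. Its gains are a variance that follows the mean, less weight on high expected counts once the baseline count is included, and a relative scale.

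**Offending is also tested by Cox regression.** This is true, and time to offence gives prolific offenders no extra weight. It limits what is at stake.

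**Custody.** A reader might infer that a participant in custody for a whole window is counted as offence-free, so that the analysis is biased against MST. The document does not say so. It says that custodial details are collected; how they are used can be left to a fuller plan. Comparing offences over a fixed window regardless of custody is a legitimate intention-to-treat contrast, and time at liberty is itself a post-randomisation quantity that treatment may change. The possible size can only be bounded by assumption. Suppose offending while at liberty is equal, placement is 30% versus 20%, a share s of placements is custodial, and a fraction f of the window is lost. The MST/MAU count ratio is then (1 − 0.20sf)/(1 − 0.30sf). With s = 0.25 and f = 0.5 it is 0.975/0.9625 = 1.01; with s = f = 1 it is 0.80/0.70 = 1.14. That supports a sensitivity analysis, not a claim of error.

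**Conclusion.** The point holds as a mismatch between stated outcome types and the stated model, for two secondary outcomes. It should be corrected, but it does not threaten the trial's main conclusion: the primary analysis and the Cox analysis are untouched, and secondary outcomes are to be interpreted with caveats.

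The cost of leaving it is an ill-suited effect scale and scale-dependent interaction tests. Invalid p-values have not been shown: the unadjusted count simulations gave 4.9% to 5.3% type I error and power within about one point, under assumed means and dispersions.

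Two further inferences are not supported:
- **Skewness.** The Background cites a cohort in which 10.2% of offenders accounted for 50.1% of offences. That is self-reported offending in a US urban cohort. It makes skewness plausible, but does not establish that 6-monthly police counts here will be mostly zero.
- **School exclusions.** They are not labelled counts, and Table 2 lists them with attendance as rates, so the point does not extend to them.

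**What to change.** Reword Statistical analysis plan, Secondary outcomes, and align the abstract with it:
- **Continuous outcomes:** keep the linear mixed models as described, and say that they apply to continuous outcomes only.
- **Offence counts:** use a repeated-measures negative binomial model, or Poisson with robust errors, with a log link, treatment-by-period terms and adjustment for the count in the 6 months before randomisation. Report rate ratios.
- **Offence-free periods:** use a repeated-measures logistic model with treatment-by-period terms. A mixed model keeps the section's missing-at-random argument; unweighted GEE generally needs a stronger assumption, so use it only if police records are near complete. Say whether the odds ratio is conditional or marginal.
- **Clustering:** use therapist-robust standard errors for both, as in the primary analysis.
- **Interactions:** test them on the scale of the named model.
- **Custody:** keep the fixed-window intention-to-treat comparison as the main analysis. Add a sensitivity analysis of counts with an offset for time at liberty, where the custody records hold usable dates. The article mentions custodial details but does not confirm that start and end dates are available.

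The cost is wording plus a little more analysis work. Effects appear as rate and odds ratios; a mean or risk difference can be reported alongside them if readers need an absolute scale. No new data collection is required, and the sample size does not change.

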### Sample size and power calculation

It is estimated that each site will have at least 140 families per year referred for treatment. On the basis of past experience, data from a meta-analysis of previous trials of MST (including major effectiveness trials from the US) that was carried out in the course of preparation of the NICE guidelines [2], and assumptions outlined below, the investigators assume that about 30% of referred families will meet the criteria and agree to randomisation; this implies that each site will be able to recruit and treat 70 to 80 families during a recruitment window of 18 months. Therefore, investigators expect to be able to recruit and assess 700 participants (350 in each arm). Figure 1 shows the expected flow of participants from recruitment through to the end of the study.

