### Moderators of outcomes

#### Therapist adherence to the multisystemic therapy model of intervention

The MST Therapist Adherence Measure-Revised (TAM-R) measures the team’s adherence to the nine MST treatment principles [50]. The TAM-R is a 28-item measure completed by parents or primary caretakers, often administered by the MST team. In the START trial it will be administered independently from the MST team by an RA not associated with that site or the families working with it. Data will be collected from the second week of MST treatment and every 4 weeks thereafter. Research has demonstrated associations between therapist adherence to the MST principles as measured by the TAM-R and youth outcomes [35,39,48,50,89-91].

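### The secondary-outcome models carry no therapist clustering; the protocol leaves therapist variance to TAM-R, an MST adherence score that cannot do that job in an MST-versus-MAU comparison

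*Protocol article*

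**What the plan says.** Three parts of the protocol article bear on how therapist effects are handled.

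- **Sample size and power calculation** (text below Figure 1). "To take account of within-therapist correlation of outcomes in the MST arm", the protocol assumes an ICC of 0.02 and 30 therapists. This gives design effects of 1.22 in MST and 1.0 in MAU, and power falls from 86% to 83%.
- **Statistical analysis plan, Primary outcome.** The logistic model is to account for clustering by therapist, and robust standard errors are named for the purpose.
- **Statistical analysis plan, Secondary outcomes.** Time to offence goes to a Cox regression. All other secondary outcomes go to linear mixed models "with separate treatment effects for the 6-, 12- and 18-month outcomes and an unstructured covariance matrix". That covariance matrix describes repeated visits on one participant. No therapist effect or clustered variance is mentioned. The section's last sentence says that there is no plan to analyse by site and that "it is hoped that TAM-R scores will pick up the variance associated with individual therapists".

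The section on therapist adherence describes TAM-R as a 28-item caregiver-completed measure of adherence to the nine MST principles. On timing it says: "Data will be collected from the second week of MST treatment and every 4 weeks thereafter".

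**The concern.** The protocol identifies a source of correlation, quantifies it and handles it for one outcome. For the rest it names a mechanism that cannot work. This is therefore more than detail left to a fuller plan.

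TAM-R is unsuitable for two reasons. First, it scores delivery of MST from the second week of MST treatment. The Management as usual section says that MAU may involve no therapy and has no comparable set of principles, so TAM-R has no counterpart there. A score that exists in one arm only cannot serve as an adjustment in the comparison of the two arms. Second, even within MST, a covariate removes only the part of the therapist variance that it happens to predict. The protocol's evidence on that is mixed: the adherence section cites associations with outcome, while the background reports that fidelity scores did not predict outcome in the Swedish trial.

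At stake is the calibration of the secondary tests and intervals. No formal multiplicity correction is planned, and nominal significance of a secondary treatment effect decides whether interaction tests are run for that outcome. Miscalibration would therefore carry into the choice of subgroup analyses.

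**Working it through.** **Inputs from the protocol:** 350 participants per arm; 30% versus 20%; ICC 0.02; 30 therapists; two-sided 0.05. The 0.05 level is stated for the primary analysis and is assumed here for the secondary Wald tests. For sensitivity, 40 therapists (10 sites with four each, from Study setting). ICCs other than 0.02 are assumptions.

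**1. Reproduce the protocol's own figures.**

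- Power without clustering: pooled rate 0.25; null SE = sqrt(0.25 × 0.75 × 2/350) = 0.0327; alternative SE = sqrt((0.21 + 0.16)/350) = 0.0325. Power = Φ((0.10 − 1.96 × 0.0327)/0.0325) = 86.5%. Stated: 86%.
- Design effect: 350/30 = 11.67 families per therapist, so DE = 1 + (11.67 − 1) × 0.02 = 1.213. Rounding up to 12 families gives 1.22, as stated.
- Power with clustering: effective MST sample 350/1.22 = 286.9; the same formula gives 82.6% (83.6% with unpooled variance). Stated: 83%.

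The planning figures are sound.

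**2. Apply the same inputs to a continuous secondary outcome analysed without clustering.** With equal variances σ² in both arms:

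- naive variance of the difference = 2σ²/350
- true variance = (DE + 1)σ²/350, because only the MST arm is clustered
- true SE / naive SE = r = sqrt((DE + 1)/2)
- true type I error = 2 × (1 − Φ(1.96/r))

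At ICC 0.02 and 30 therapists, r = sqrt(2.213/2) = 1.052. The naive SE is too small by 1 − 1/1.052 = 4.9%, and the type I error is 2 × (1 − Φ(1.863)) = 6.2%.

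| Therapists | ICC | DE | r | SE too small by | True type I error |
|---|---|---|---|---|---|
| 30 | 0.01 (assumed) | 1.107 | 1.026 | 2.6% | 5.6% |
| 30 | 0.02 (protocol) | 1.213 | 1.052 | 4.9% | 6.2% |
| 30 | 0.05 (assumed) | 1.533 | 1.126 | 11.1% | 8.2% |
| 30 | 0.10 (assumed) | 2.067 | 1.238 | 19.2% | 11.3% |
| 40 | 0.02 (protocol) | 1.155 | 1.038 | 3.7% | 5.9% |

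**3. Check by simulation.** With 20,000 runs of an unclustered two-arm comparison, rejection rates under the null were 6.1% (30 therapists, ICC 0.02), 8.2% (30, 0.05), 11.4% (30, 0.10) and 5.8% (40, 0.02), in line with the formula.

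The formula is for one continuous comparison with complete data. It was not derived for the Cox model.

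**The case against.** **The effect is small and the outcomes are secondary.** At the planned ICC the excess is about one percentage point of type I error, and the protocol promises caveats when secondary effects are interpreted. This stands, and it limits the weight of the point.

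**The robust-variance sentence may be meant for every model.** It is worded generally. But it sits under Primary outcome, directly after that outcome's interaction tests, and Secondary outcomes does not repeat it. If it did apply throughout, the closing hope about TAM-R would be unnecessary and confusing. Either way the text needs correcting.

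**The TAM-R sentence is vague.** It is not expressly limited to secondary outcomes. A reader might infer that TAM-R will be a covariate in the between-arm models, so that they condition on a post-randomisation variable, or that a TAM-R-by-arm interaction will be tested because TAM-R appears under Moderators of outcomes. The protocol specifies neither. The interactions it names for the primary outcome are gender, age, criminal record and referral path. What stands is that TAM-R is the only thing offered for therapist variance at the end of the section, and that it is unsuitable for that. That TAM-R exists only in MST is itself an inference from what it measures and when; no sentence says so.

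**Every secondary p-value is too optimistic.** A reader might infer this, but the documents do not support it. Inflation needs a positive therapist ICC for each outcome, and the only ICC given was assumed for out-of-home placement. There is also a possible offset. Allocation is minimised on centre, gender, age and age at onset, and a model that omitted those factors would tend to overstate the SE. Against a variance ratio of 1.107, factors explaining roughly 11% of outcome variance (an assumed figure) would cancel the inflation.

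**The models omit baseline scores and minimisation factors.** This too might be inferred, but it rests only on silence in a condensed article. Covariate lists for secondary models are commonly left to the full plan, so it forms no part of this point.

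**Conclusion.** The point holds in a limited form. The protocol recognises therapist clustering, handles it for the primary outcome, states secondary models without it, and puts its hope in a measure that cannot stand in for a cluster term across arms. For a continuous outcome at the protocol's inputs, the SE is about 5% too small and the true type I error about 6.2% rather than 5%, or 5.9% with 40 therapists. The range of about 5.6% to 11.3% rests on assumed ICCs of 0.01 to 0.10 with 30 therapists.

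These figures assume a therapist ICC above 0, equal variances, near-equal caseloads, a nominal two-sided 0.05 level and no offset from omitted balancing factors. No figure is claimed for the Cox model. The primary result is not affected. The change should be made because the inconsistency is plain and the remedy cheap, not because the expected distortion is large.

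**What to change.** In the Secondary outcomes part of the analysis plan:

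1. Add a therapist random effect, in the MST arm only, to the linear mixed models, alongside the unstructured covariance over visits.
2. Use therapist-clustered robust variance for the Cox model, with each MAU participant as a cluster of one.
3. Delete the TAM-R sentence as a way of handling clustering, and report TAM-R as an association between adherence and outcome within the MST arm.

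This brings the secondary analyses into line with the sample-size assumptions and the primary analysis. It needs therapist identity for each MST participant, which the primary analysis already requires. The cost is slightly wider intervals on secondary outcomes, by about 5% at the protocol's ICC with 30 therapists.
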